# Preventing Respiratory Viral Illness Invisibly (PRiVII): protocol for a pragmatic cluster randomized trial evaluating far-UVC light devices in long-term care facilities to reduce infections

**DOI:** 10.1186/s13063-024-07909-0

**Published:** 2024-01-26

**Keywords:** Respiratory viral illness, Long-term care, Cluster randomized controlled trial, Geriatrics

## Abstract

**Background:**

Respiratory viral illness (RVI)—e.g., influenza, COVID-19—is a serious threat in long-term care (LTC) facilities. Standard infection control measures are suboptimal in LTC facilities because of residents’ cognitive impairments, care needs, and susceptibility to loneliness and mental illness. Further, LTC residents living with high degrees of frailty who contract RVIs often develop the so-called atypical symptoms (e.g., delirium, worse mobility) instead of typical cough and fever, delaying infection diagnosis and treatment. Although far-UVC (222 nm) light devices have shown potent antiviral activity in vitro, clinical efficacy remains unproven.

**Methods:**

Following a study to assay acceptability at each site, this multicenter, double-blinded, cluster-randomized, placebo-controlled trial aims to assess whether far-UVC light devices impact the incidence of RVIs in LTC facilities. Neighborhoods within LTC facilities are randomized to receive far-UVC light devices (222 nm) or identical placebo light devices that emit only visible spectrum light (400–700 nm) in common areas. All residents are monitored for RVIs using both a standard screening protocol and a novel screening protocol that target atypical symptoms. The 3-year incidence of RVIs will be compared using intention-to-treat analysis. A cost-consequence analysis will follow.

**Discussion:**

This trial aims to inform decisions about whether to implement far-UVC light in LTC facilities for RVI prevention. The trial design features align with this pragmatic intent. Appropriate additional ethical protections have been implemented to mitigate participant vulnerabilities that arise from conducting this study. Knowledge dissemination will be supported through media engagement, peer-reviewed presentations, and publications.

**Trial registration:**

ClinicalTrials.gov NCT05084898. October 20, 2021.

**Supplementary Information:**

The online version contains supplementary material available at 10.1186/s13063-024-07909-0.

## Introduction

### Background and rationale {6a}

For decades, respiratory viral illness (RVI) has been recognized as a serious hazard for long-term care (LTC) facility residents [1]. The COVID-19 pandemic has underscored this vulnerability; LTC residents account for over 40% of all COVID-19 deaths in Canada [2].

Standard infection control interventions, including handwashing, physical distancing, and personal protective equipment [3, 4], have proved to be suboptimal in LTC for several reasons. First, dementia and frailty can impair adherence to handwashing and physical distancing recommendations. Second, many residents need intimate personal care, thereby obliging close proximity [5–7]. Third, physical distancing can exacerbate residents’ susceptibility to loneliness and mental illness [8, 9].

Far-UVC light (222 nm) could help to address the shortcomings of standard infection control interventions. Far-UVC light can kill a variety of microbes in vitro, including influenza viruses and SARS-CoV-2 [10–12], without damaging human tissues [13–15]. Further, far-UVC light can effectively kill airborne microbes in a full-sized room, even with continuous introduction of microbes into the space [16]. As this intervention does not require active adherence, it could provide a valuable layer of protection of LTC residents. Despite mounting evidence of in vitro efficacy, to our knowledge, no clinical trials have been conducted to evaluate the effectiveness of far-UVC at reducing the incidence of RVIs in clinical settings, including LTC facilities.

Capturing all RVIs will be important for determining the efficacy of far-UVC light in this trial. For this reason, it is important to recognize that RVIs, including COVID-19, often present “atypically” in frail older adults [17, 18]. Illness in these patients may present with delirium, but without associated cough or fever [18–20]. In short, an “atypical presentation” in many people is how illness typically presents in older adults who live with frailty [21]. Atypical presentations can cause standard screening protocols to yield false negatives, delaying diagnosis, treatment, and more stringent infection control interventions (e.g., isolation). To capture RVIs as early as possible in the trial, three additional screening tools: the single question in delirium (SQiD), the single question in reduced mobility (SQiRM), and the single question in function (SQiF) will be used. The SQiD asks: “Is the patient more confused than before?” [22] and has been validated in clinical settings [22–24]. Building on the principles of the SQiD, the SQiRM and the SQiF evaluate changes in mobility and overall function, respectively. SQiRM and SQiF are novel screening tools.

### Objectives {7}

The Preventing Respiratory Viral Illness Invisibly (PRiVII) trial is a pragmatic cluster randomized trial that aims to answer the following question: Should far-UVC light be used in LTC facilities to help reduce the incidence of RVIs? The trial has completed Phase 1. This article describes the protocol for Phase 2 of the trial, which includes updated far-UVC light devices and a third LTC facility study site. Prior to the trial, stakeholder engagement was conducted to ensure that study procedures were compatible with the LTC facility setting and to promote the autonomy, welfare, and justice interests of participants and associated parties [25].

### Trial design {8}

This is a multicenter, double-blinded, cluster randomized, placebo-controlled, superiority trial with two parallel arms. The protocol is registered on ClinicalTrials.gov: registration number NCT05084898. It has pragmatic intent; it aims to inform clinical decisions of whether far-UVC light should be implemented in LTC facilities to reduce the incidence of RVIs. Cluster randomization is necessary because placing far-UVC lights in common areas constitutes a cluster-level intervention.

## Methods

### Study setting {9}

Two LTC facilities in Nova Scotia were included in Phase 1 of the trial. In Phase 2, a third LTC facility was added. The trial flow chart is reported in Fig. 1.

**Fig. 1 Fig1:**
[figure not shown]
Trial flow chart

In Phase 1 of the trial, two LTC facilities in Nova Scotia were selected: one in Halifax and one in Falmouth. These locations vary in many aspects, including building type, layout, and size. The layout of the Halifax LTC facility is similar to an acute care ward and has semi-private rooms (private bedroom with shared bathrooms) and shared bedrooms (shared by two residents), whereas the layout of the Falmouth LTC facility is similar to a large house and has private bedrooms and private bathrooms. These sites were selected for the study as a result of feasibility and logistical constraints. There are four participating neighbourhoods at the Halifax LTC facility and two participating neighbourhoods at the Falmouth LTC facility. There are 18–36 residents living in each neighborhood.

In Phase 2, a LTC facility in Cape Breton, Nova Scotia, was added to the trial. It has private bedrooms with private bathrooms and semi-private rooms. There are five participating neighborhoods in this LTC facility.

### Eligibility criteria {10}

All residents in participating neighborhoods in each LTC facility are eligible for study participation. In Nova Scotia, people may only move into LTC facilities if they are medically stable and have nursing needs that cannot be met through home care. Therefore, frailty and dementia are highly prevalent in LTC facilities [26]. LTC facility staff are ineligible to participate because they routinely travel between neighborhoods within LTC facilities and therefore cannot be randomized. LTC facility visitors are ineligible because of the likelihood of exposure to RVIs outside of the LTC facilities.

### Who will take informed consent {26a}

Research nurses at each LTC facility seek informed consent from all LTC facility residents or their substitute decision-maker (SDM) for study data collection.

### Additional consent provisions for collection and use of participant data and biological specimens {26b}

Participant data will not be used in ancillary studies.

## Interventions

### Explanation for choice of comparator {6b}

LTC facility neighborhoods randomized to the control arm receive standard disinfection procedures and are subject to Nova Scotia’s mandated COVID-19 prevention measures and infection prevention and control guidelines. These consist in personal protection equipment, cleaning and sanitizing, physical distancing, and restrictions on visitors and nonessential personnel [27]. These guidelines fluctuate depending on COVID-19 outbreaks in the province and are expected to vary during the study. Placebo light devices that are identical to the far-UVC light devices but emit only visible spectrum light (400–700 nm) are installed in common areas (hallways, living rooms, and dining rooms). The clinical effectiveness of the intervention has not been proven in previous clinical trials; therefore, a placebo control—in combination with usual care infection control measures—is justified.

### Intervention description {11a}

LTC facility neighborhoods randomized to the intervention arm receive far-UVC light devices in addition to mandated infection control interventions. The far-UVC light devices are approximately the size of a smoke detector. They are installed on the ceiling in high traffic common areas in LTC facilities, where residents spend approximately 3 to 4 h per day. The lights are on 24 h per day throughout the data collection period of the study. The devices produce no heat, and the only indicators of operation are an indicator LED and a dim blue light from a square in the center.

At the onset of Phase 1, the threshold limit value (TLV) set by the American Conference of Governmental Industrial Hygienists (ACGIH) for 222-nm far-UVC was 23 mJ/cm^2^ per 8-h working day. The far-UVC devices used in Phase 1 emit 222-nm light, at an 80° beam angle, with an output tuned to meet this TLV at a height of 2.1 m from the floor for a standard 2.7-m ceiling. Since the start of Phase 1, ACGIH has updated 222-nm far-UVC TLVs to 160 mJ/cm^2^ per 8 h for eye exposure and 479 mJ/cm^2^ per 8 h for skin exposure [28].

The American National Standards Institute (ANSI) and Illuminating Engineering Society (IES) have adopted ACGIH’s new TLVs in their ANSI/IES RP-27.1–22 standard. To reflect these updated photobiological limits, the far-UVC devices will be replaced in Phase 2. The new devices (1) emit higher irradiance to achieve higher doses than Phase 1, (2) are equipped with an optical filter to attenuate UVC wavelengths above 23 nm, and (3) are equipped with a diffuser to increase the beam angle to 108°.

### Criteria for discontinuing or modifying allocated interventions {11b}

Far-UVC light in common areas is a cluster-level intervention. Therefore, it is infeasible to modify it for an individual participant. Based on previous studies, it is anticipated to pose minimal risk to participants.

### Strategies to improve adherence to interventions {11c}

Far-UVC light does not require participants to actively adhere. Participants will be free to use common areas as much as they wish, in keeping with the trial’s pragmatic intent.

### Relevant concomitant care and interventions that are permitted or prohibited during the trial {11d}

Throughout the trial, participants in the intervention and control arm all receive usual care, including standard disinfection control measures.

### Provision of posttrial care {30}

After the trial, participants will continue to receive usual care.

### Outcomes {12}

The primary outcome is the incidence of RVIs, diagnosed from nasopharyngeal swabs. RVIs include SARS-CoV-2, influenza A, influenza B, and other upper respiratory viruses, depending on epidemiology and mandated testing protocols.

Secondary outcomes include the incidence of erythema and photokeratitis among LTC residents; the sensitivity, specificity, positive predictive value, negative predictive value, and validity of SQiD, SQiRM, and SQiF for identifying RVIs, and the value for money for the implementation of the far-UVC infection control strategies. The SQiD has been validated as a screening tool for delirium in geriatric inpatients and oncology inpatients [23, 24]. It has not been validated in LTC homes. The SQiRM and the SQiF have not been validated—they will be assessed for the first time in this trial.

Exploratory outcomes include the severity of RVI (oxygen requirements, recovery rates, and time to recovery or death). The outcomes in Phase 2 are unchanged from Phase 1.

### Participant timeline {13}

LTC facility residents are approached by research staff to inform them about the trial and seek consent for data collection. For residents living in the LTC facilities prior to study onset, this occurred before the onset of the trial. Whenever a new individual moves into a participating LTC home, they will be approached shortly after moving in. Residents undergo daily assessments as part of routine care, and their data is collected by nurses working in the facility. The timeline is summarized in Table 1.

**Table 1 Tab1:**
[figure not shown]
SPIRIT diagram

### Sample size {14}

Prior to Phase 1, sample size estimations were limited by uncertainty surrounding the expected incidence of SARS-CoV-2 in the study setting. The approach taken here was to include as many clusters as feasibly possible given budget and logistical constraints, and then estimate the necessary sample size 1 year into the study.

The sample size was determined using a log-rank test comparing two survival rates in a cluster randomized design. The intra-class correlation coefficient (ICC) for the neighborhoods and the survival probability for the entire sample was calculated using the data collected by year 1. The survival probability should be calculated for just the control group; however, using the entire sample enabled the primary biostatistician to remain blinded, which is the recommended practice [29–31]. Theoretically, this approach would lead us to overestimate the necessary sample (if we assume the treated group had less or equal cases to the control group).

At the time of the interim analysis, there were 178 participants in the trial (20–25 per cluster), and the median time in the study was 0.98 years (*IQR*: 0.49–1.02). There were 30 cases resulting in an incidence rate of 0.22 (95% *CI*: 0.15–0.31). The ICC was estimated using a random effects logistic regression model [32], but the low incidence rate meant the estimate was not reliable (*ICC* = 0.12, 95% *CI*: 0.002–0.883). We believe that our incidence rate estimate of 0.22 cases per year is low and unlikely to represent the future rates of infection because of the changes in prevention strategies since the first year of data collection. We have therefore modelled several scenarios where we vary the survival probability between 0.4 and 0.7 (Additional File 1).

The fixed parameters used were power at 0.8, alpha at 0.05, the number of clusters in the experimental and placebo groups (3 in control and 3 in the treatment), and a hazard ratio of 0.7. Analysis was completed using the Stata’s *power logrank, cluster* command. We attempted to include varying levels of ICC; however, our sample size estimates were very sensitive to the ICC and could not actually be estimated with our parameters specified above. Without accounting for the ICC, we would require between 470 and 968 participants if the survival probability in the control group was 0.4 or 0.7 respectively. At the time of this calculation, we anticipated recruiting a maximum of 250 participants within our timeline, which would likely leave us underpowered. Based on these results, we added an additional site (five more clusters) and extended the study by a year (i.e., Phase 2). With these modifications, we anticipate being able to recruit approximately 500 persons into the study. We will conduct another interim analysis at year 2 of the study to determine if these modifications will suffice. At that time, we anticipate being able to define our survival probability more accurately and properly account for the ICC in the sample size calculation.

### Recruitment {15}

To recruit participants, all LTC facility residents or their SDMs are approached by research nurses at each LTC facility.

## Assignment of interventions: allocation

### Sequence generation {16a}

Randomization is at the level of “neighborhoods” within LTC facilities (distinct areas within LTC facilities that house social groups of 18–36 residents). In Phase 1, neighborhoods in the Halifax and Falmouth LTC facilities, 16 in total, were randomized with a 1:1 allocation ratio. In Phase 2, five neighborhoods were randomized in the Cape Breton LTC facility: two to the placebo arm and three to the active arm. Randomization is stratified by LTC facility. Randomization was performed by a blinded biostatistician who is otherwise uninvolved with the study using SAS 9.4 software. 

### Concealment mechanism {16b}

The biostatistician communicated the neighborhood assignment to the sole unblinded study coordinator, who then facilitated the installation of placebo and intervention light devices.

### Implementation {16c}

The biostatistician generated the allocation sequence and communicated it to the unblinded study coordinator. The unblinded study coordinator then worked with blinded LTC facility administrators to coordinate the installation of the UVC and placebo light devices.

## Assignment of interventions: blinding

### Who will be blinded {17a}

The far-UVC lights are indistinguishable from the placebo lights. LTC facility residents, LTC facility staff, on-site researchers, and the biostatistician performing the analysis are blinded to group allocation. Only two members of the research team are unblinded to coordinate light installation by an independent third-party contractor. Blinded team members do not have access to participants’ identifiable information.

### Procedure for unblinding if needed {17b}

Emergency envelopes containing the randomization allocation are stored in two locations: a locked drawer in the study coordinator’s office and the unblinded study coordinator carries the second envelope on her during work hours. In case of serious adverse event, the study coordinators are able to facilitate unblinding.

## Data collection and management

### Plans for assessment and collection of outcomes {18a}

Participant information, including demographics (e.g., age, sex, ethnicity), health status (e.g., presence of chronic diseases, a Frailty Index calculated from the resident Comprehensive Geriatric Assessments routinely completed twice a year [33], smoking status, verbal/non-verbal), vaccination status for influenza and COVID-19, and emotional/social support (number of visitors, time spent telecommunicating with family or friends) are collected from medical records and a baseline history and physical exam conducted by research nurses at the time of enrollment. Residents in participating neighborhoods who do not consent to data collection are included from RVI case counts, and only their neighborhood, age, and sex are collected from their medical records.

The novel screening protocol is administered daily to residents in both study arms. This includes assessment using the SQiD, SQiRM, and SQiF in addition to the standard screening protocol for infectious symptoms. The SQiD, SQiRM, and SQiF are single question assessments with binary outcomes. The SQiD asks: “Is the patient more confused than before?” The SQiRM asks: “Is the person’s mobility worse (reduced) compared with before (in the last 24 hours)?” and the SQiF asks: “Is the person’s functioning worse than before (in the last 24 hours)?” Compared to a psychiatric interview, the SQiD has a sensitivity of 80% (95% CI 28.3– 99.49%), a specificity of 71% (41.90–91.61%), a positive predictive value of 50%, and a negative predictive value of 91% (58.72–99.77%) [22]. It has been validated in geriatric inpatients and oncology inpatients but has not been validated in LTC homes. The SQiRM and SQiF will be evaluated for the first time in this trial.

If any of the SQiD, SQiRM, or SQiF yield a positive finding, then the resident is assessed with the 4 A’s test (4AT) and Hierarchical Assessment of Balance and Mobility (HABAM) screening every day for 4 days or until a new stable baseline is established (defined as consistent 4AT and HABAM for 7 consecutive days). If positive on 4AT, HABAM, or standard screening protocol, the resident receives a nasopharyngeal swab for respiratory viruses.

In this trial, the 4AT and HABAM are used as process measures to help evaluate the clinical utility of the SQiD, SQiRM, and SQiF. The 4AT is a screening tool for delirium, typically used in conjunction with the SQiD. It requires the assessor to evaluate the patient’s alertness and the acuity of the change in mental status, and ask questions that evaluate orientation (e.g., age, date of birth, place, current year) and attention (e.g., list the months in reverse order). The 4AT has been validated for clinical use, with a sensitivity of 89.7% and specificity of 84.1% when compared to a psychiatric diagnosis of delirium [34]. The 4AT has been validated for use in assessing older adults [34–36]. The HABAM is a clinical tool used to assess patient in-bed mobility, transfers, and ambulation [37]. Given the sensitivity of HABAM dynamics to important clinical outcomes in hospital [38], more recently, it has been used to track the course of delirium, as it may offer a more stable estimate than does attention [39–41]. The HABAM has been used in geriatric medicine patients in both inpatient and outpatient settings but not explicitly in LTC homes [42].

The incidence of erythema and photokeratitis is collected via daily routine physical exams conducted by LTC facility staff.

If a resident tests positive for an RVI, their vital signs are collected daily via routine physical exam until they recover or die. All-cause mortality is collected from medical records by research nurses. Data collection in Phase 2 is unchanged from Phase 1.

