#### Secondary analysis

To assess the inter-rater reliability of the novel RVI screening protocol, prior to the trial, two research nurses assessed every participant once every 7 days, and concordance between raters was tracked. We will explore inter-rater agreement of each component (SQiD, SQiF, SQiRM, 4AT, and HABAM) using several agreement coefficients and their 95% confidence intervals, including percent agreement, kappa, Fliess’s kappa, Gwet’s AC, and Krippendorff’s alpha coefficient. Analysis will be carried out using Stata package *kappaetc* which follows methods and formulas discussed in Gwet [45]. We will also look at the sum of scores for SQiD, SQiF, and SQiRM and determine agreement for the overall score using the above measure and possibly ICC using a two-way mixed-effects model, provided model assumptions are met.

To assess the validity of the novel RVI screening protocol, the sensitivity, specificity, positive predictive value, and negative predictive value will be compared to the standard RVI screening protocol. Additionally, concordance between answers on the SQiD, SQirM, SQiF, 4AT, and HABAM will be tracked to determine if any questions are capturing otherwise undetected information.

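### The described swab depends on the screening result, so the planned accuracy of the SQiD, SQiRM and SQiF for RVI is subject to partial verification bias

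*Protocol article*

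**What the plan says.** In the protocol article, Outcomes {12} lists as a secondary outcome "the sensitivity, specificity, positive predictive value, negative predictive value, and validity of SQiD, SQiRM, and SQiF for identifying RVIs". The same section fixes the reference standard: "The primary outcome is the incidence of RVIs, diagnosed from nasopharyngeal swabs".

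Plans for assessment and collection of outcomes {18a} sets out how a resident comes to be swabbed. The novel protocol is given daily in both arms: "This includes assessment using the SQiD, SQiRM, and SQiF in addition to the standard screening protocol for infectious symptoms". The gate to the second stage is: "If any of the SQiD, SQiRM, or SQiF yield a positive finding, then the resident is assessed with" the 4AT and HABAM. The swab rule is then: "If positive on 4AT, HABAM, or standard screening protocol, the resident receives a nasopharyngeal swab for respiratory viruses".

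Under Statistical methods {20a}, Secondary analysis says that, for the novel protocol, "the sensitivity, specificity, positive predictive value, and negative predictive value will be compared to the standard RVI screening protocol". It does not say how residents without a swab enter these measures.

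**The concern.** Sensitivity, specificity and NPV need the true RVI status of residents who screen negative as well as positive. Here the tests under evaluation decide who gets the reference test. Two groups have no described swab:

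- residents negative on all three questions and on the standard screen;
- residents positive on a question but negative on 4AT, HABAM and the standard screen.

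Infections in these groups drop out of the sensitivity denominator, and their non-infections are either missing or assumed. The novel protocol also contains the standard one, so the direction of their sensitivity comparison is settled before any data arrive.

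The article presents this as the first assessment of the SQiRM and SQiF. If overstated sensitivity were published, facilities could place more trust in a negative answer for a frail resident than the data justify.

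**Working it through.** **The plan's own accuracy figures.** Only the SQiD has any, against psychiatric interview. The smallest matching counts (inferred) with exact intervals reproduce them: 4/5 = 80% (28.36 to 99.49), 10/14 = 71.4% (41.90 to 91.61), 4/8 = 50%, 10/11 = 90.9% (58.72 to 99.77). The printed lower limit of 28.3 is a truncation. These figures concern delirium and cannot be carried over to RVI, for which the article states no expected accuracy.

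**Inputs (all assumed; base case).** Prevalence per assessment p = 5%; question sensitivity a = 50% and specificity b = 90%; standard screen sensitivity s = 50% and specificity t = 95%; chance that 4AT or HABAM is positive after a positive question, c1 = 80% with RVI and c0 = 30% without. Question and standard screen are taken as independent given RVI status, and the question as the only gate to 4AT/HABAM.

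**Swab rule from {18a}.** The chance of a swab is 1 if the standard screen is positive, c if only the question is positive, and 0 if both are negative.

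**Sensitivity of a question.**
Observed = a[s + (1−s)c1] / {a[s + (1−s)c1] + (1−a)s}
= 0.5 × 0.9 / (0.5 × 0.9 + 0.5 × 0.5) = 0.45/0.70 = 64.3%, against a true 50%.
With s = 20%: 0.42/0.52 = 80.8%. With s = 80%: 0.48/0.88 = 54.5%.

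**Specificity, PPV and NPV of a question.**
- Swabbed without RVI, as a share of all without RVI: question-positive 0.1 × (0.05 + 0.95 × 0.3) = 0.0335; question-negative 0.9 × 0.05 = 0.045.
- Swabbed only: specificity 0.045/0.0785 = 57.3%; PPV 0.0225/(0.0225 + 0.031825) = 41.4%; NPV 0.04275/(0.04275 + 0.0125) = 77.4%.
- Unswabbed counted as RVI-free (question-positive share 0.12, question-negative 0.88): specificity 0.8675/0.965 = 89.9%; PPV 0.0225/0.12 = 18.8%; NPV 0.8675/0.88 = 98.6%.

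| | True | Swabbed only | Unswabbed = RVI-free |
|---|---|---|---|
| Sensitivity | 50.0 | 64.3 | 64.3 |
| Specificity | 90.0 | 57.3 | 89.9 |
| PPV | 20.8 | 41.4 | 18.8 |
| NPV | 97.2 | 77.4 | 98.6 |

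**Range.** There were 729 scenarios: p 1 to 20%, a 30 to 80%, b 71 to 95%, s 20 to 80%, c1 50 to 100%, c0 10 to 50%. Observed sensitivity was too high in all of them, by 2 to 38 points, and lay between 33% and 95%. Swabbed-only specificity was 8 to 52 points too low, and NPV 1 to 60 points too low. With the unswabbed counted as RVI-free, specificity moved by −7 to +4 points and NPV rose by 0 to 16.

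**Two simplifications.** First, with three questions, a case negative on one may reach 4AT/HABAM through another. If that happens with probability m, the false-negative term becomes (1−a)[s + (1−s)m·c1]. The base case then gives 64.3% at m = 0, 0.45/(0.45 + 0.35) = 56.3% at m = 0.5, and 50% at m = 1. The size shrinks, but the direction stays. Second, if question and standard screen are not independent, the upward direction needs question-positive cases to be swabbed more often than question-negative ones. With c1 = 80%, question-positive cases are swabbed at least 80% of the time, so this holds while the standard screen catches fewer than 80% of question-negative cases.

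**Combined protocol against standard.** Of all cases, the standard screen finds 50%; adding the question-then-4AT/HABAM pathway finds 0.45 + 0.25 = 70%. Among cases found, the combined protocol reads 70/70 = 100% and the standard screen 50/70 = 71.4%. Both absolute figures are wrong, but their ratio is 1.40 in truth and as observed.

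**Why relative measures work.** Everyone positive on the pathway or on the standard screen is swabbed. For pathway against standard, the relative true-positive fraction is (0.5 × 0.8)/0.5 = 0.80 and the relative false-positive fraction is (0.1 × 0.3)/0.05 = 0.60, both free of the missing cells. The pathway's extra RVIs are 0.05 × 0.5 × 0.8 × 0.5 = 0.0100 and its extra negative swabs 0.95 × 0.1 × 0.3 × 0.95 = 0.0271, so 0.0100/0.0371 = 27 RVIs per 100 extra swabs.

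**The case against.** The strongest reply is that the standard screen is a separate route to a swab. A resident negative on all three questions but positive on the standard screen is swabbed and, if infected, counts as an observed false negative for each question. That stands: verification is partial, not complete. A reader might infer that the accuracy of each question will look near-perfect by construction. The documents do not support this. A value of 100% is forced only for the combined protocol, and specificity is lowered or left roughly right, not inflated.

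A reader might also infer that residents are swabbed solely after a positive screen. The article does not say so, and it defines the viruses counted as "depending on epidemiology and mandated testing protocols". Mandated testing may supply swabs in screen-negative residents, though none is described.

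Nor is the whole comparison with standard screening settled in advance. Nesting fixes the direction of the sensitivity and specificity differences, but not the size of the gain or its cost in false positives. The planned concordance analysis, which asks whether a question picks up something the others miss, is already close to an added-yield measure.

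Finally, the handling of unswabbed residents may sit in an analysis plan not shown. Such a plan could choose a convention or a correction, but it could not recover the missing swabs without assumptions. Using the standard screen itself as the reference would not help, since Background and rationale {6a} says: "Atypical presentations can cause standard screening protocols to yield false negatives".

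**Conclusion.** The point holds as partial verification bias. Followed as described, the plan overstates the sensitivity of a single question: 50% reads as about 64% in the base case, and the excess is 2 to 38 points over the assumed range. The excess is smaller where the other questions also lead to 4AT/HABAM. Sensitivity of the combined protocol is 100% by construction among cases found by this route. Specificity is too low among swabbed residents and roughly right if the unswabbed are counted as RVI-free; PPV and NPV also shift with that choice.

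All sizes rest on assumed prevalences and accuracies, because the article gives none for RVI. The upward direction rests on question-positive cases being swabbed more often than question-negative ones.

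This is a secondary outcome. The same screening is given in both arms, and nothing here shows an effect on the primary far-UVC comparison, so that should not be inferred.

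**What to change.** Change the analysis wording; no extra swabs are needed.

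1. Make the reported comparison of the question-then-4AT/HABAM pathway with standard screening consist of PPV per swab, extra RVIs found per 100 extra swabs, and relative true-positive and false-positive fractions. Cluster standard errors by resident, because screening is daily.
2. Report absolute sensitivity, specificity and NPV of the SQiD, SQiRM and SQiF only in swabs taken regardless of screening result, if mandated testing supplies any. Otherwise give verification-bias-corrected estimates with the assumptions and a sensitivity range. Reweighting alone will not do: residents negative on everything have no described chance of a swab, so their RVI prevalence has to be assumed and varied.
3. State how unswabbed residents are counted wherever PPV, NPV or specificity is shown.

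The cost is that unqualified absolute accuracy is no longer claimed. The relative measures also describe the gated pathway, so each question taken alone is assessed only through item 2 and the concordance analysis already planned.
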